# Abbreviations/Acronyms

BP: Blood pressure

CMRFs: Cardiometabolic risk factors

CHW: Community health workers

CVD: Cardiovascular diseases

DASH: Dietary approaches to stop hypertension

IPAQ: International physical activity questionnaire

GEE: Generalized estimating equations

LMICs: Low- and Middle-Income Countries

National Commission for Science Technology and Innovation

NCDs: Non-communicable diseases

SSA: Sub Saharan Africa

RCT: Randomized controlled trial

WHO: World Health Organization

# Abstract

In Sub Saharan Africa (SSA) there is a growing burden of Non communicable diseases (NCDs) which poses a big challenge to the weak health system in these resource limited settings. As governments prioritize the control of the COVID 19 pandemic, consequences of chronic diseases such as cardiometabolic risk factors (CMRFs) continue unabated. The aim of this study is to explore innovative strategies to improve blood pressure and body composition through community health workers lifestyle interventions among hypertensive patients in low income populations of Kiambu County, Kenya.

This will be a community-based study which will begin with home-based blood pressure(BP) screening by community health workers (CHW). Those identified as hypertensive will then be recruited to a randomized control trial. The randomized controlled trial (RCT) will involve 52 hypertensive patients willing to be followed up for 6 months. The patient will be randomised to either CHW led lifestyle intervention or usual care arm. The intervention will be implemented for 6 months with outcome assessment at 3 and 6 months. The recruitment will be conducted in level 3 primary health care facilities in Juja and Ruiru Sub-counties in Kiambu County.

An adapted WHO stepwise questionnaire will be used to collect information on demographic characteristics, history of hypertension, other cardiovascular disease (CVD) risk factors, and health behaviours participants at baseline and follow-up visits. The international physical activity questionnaire (IPAQ) will be used to collect data on physical activity. To assess the outcome of the intervention survey will be conducted at baseline, 3 months and 6 months. The research assistants will be blinded to the randomization status of the participants. We will use STATA version 15 software for statistical analyses. The differences between the control and intervention groups on baseline demographics, biological and behavioral measures will be assessed using nonparametric (Wilcoxon rank-sum test, chi square test) and parametric tests(t-test) as appropriate. Generalized estimating equations (GEE) approach will be used to analyze how BP vary over the six months after adjusting for intervention group. This study will not only provide an innovative approach to the management of hypertension through CHW primary health prevention but will also provide preliminary data on feasibility and acceptability of integrating CHW in the control of hypertension for a future fully- powered RCT.

# BACKGROUND INFORMATION

Globally, the COVID-19 pandemic is taking an enormous toll on public health with the priority being to control the pandemic. As governments prioritize the control of the pandemic, consequences of chronic diseases such as cardiometabolic risk factors (CMRFs) continue unabated (Brook et al., 2020). Studies have documented a high mortality and morbidity from other causes as an indirect effect of COVID-19 pandemic resulting from the lack of routine preventative care, delays in diagnosis of new diseases and disruptions to treatment of chronic conditions.

Cardiometabolic risk factors account for the largest proportion of global mortality(Yusuf et al., 2020). The proportion of controlled hypertension is also low, especially in Low and Middle Income Countries (LMICs) with only 7.7% of patients with hypertension having controlled blood pressure (BP) (<140/90 mmHg) in LMICs(Mills et al., 2016). In Sub Saharan Africa (SSA) there is a growing burden of Non communicable diseases (NCDs) which poses a big challenge to the weak health system in these resource limited settings(Moucheraud, 2018). Further, management of cardiovascular diseases (CVDs) in low resource settings is challenging due to limited human and financial resources. There is a need for research to explore innovative, cost effective, and contextually relevant interventions to control BP levels and other cardiovascular risks factors as well as the associated morbidity and mortality in LMICs("Poster Abstracts from the 7th Annual CUGH Conference: Bridging to a Sustainable Future in Global Health," 2016) even in the midst of COVID-19 pandemic.

The dual burden of infectious and NCDs in SSA requires innovative and sustained investment in primary health interventions. Community health workers (CHWs) are a low-cost integral part of health-care delivery system in Kenya and other LMICs. With the shortage of health workers, CHWs have the potential to supplement the formal health system in the struggle to achieve universal health coverage in the era of dual burden of infectious diseases and NCDs in Kenya and other LMICs. Community health workers have been used effectively in the developed world for the management and control of hypertension(Perry et al., 2014). CHW may remove barriers to BP control and medication adherence due to cultural, educational, and language differences between community members and the health care system(Brownstein et al., 2005). A systematic review on the effectiveness of CHW interventions for management of hypertension in the United States showed significant improvement in BP control particularly among the poor, urban minority communities(Brownstein et al., 2007). Similarly, community health workers home-based interventions have shown positive impact in the management and control of hypertension in LMICs (Cappuccio et al., 2006; He et al., 2017; T. Jafar et al., 2009; Neupane et al., 2018; Vedanthan et al., 2019).

One of the ways to address the emerging burden of hypertension could be through home BP monitoring and lifestyle interventions led by CHW. Home BP monitoring has been proven as an effective tool in the management of hypertension(Glynn et al., 2010; Pickering et al., 2008). Compared to measurements in a health facility, home BP monitoring minimizes the “white coat” effect and allows for frequent and multiple readings(Stergiou & Bliziotis, 2011; Verberk et al., 2005) which provides additional BP measurements leading to better treatment decisions. It has been shown that use of electronic cuffs for home BP monitoring is more effective in reaching target BP reduction goals than BP monitoring in a clinical setting alone (Cappuccio et al., 2004) and when combined with other intervention such as patients education and lifestyle counselling is associated with even better BP control(Tucker et al., 2017).

**1.1 Problem statement**

Hypertension is the leading risk factor for deaths due to CVDs and as such, the World Health Organization (WHO) targets to have a worldwide 25% reduction in the prevalence of hypertension by the year 2025 (World Health Organization, 2014). The STEPwise survey shows 24% of Kenyans either had elevated BP or were on treatment for hypertension. Only 8% of the hypertensive persons were on treatment, and among them, only 4.6% had controlled BP (Kenya Ministry of Health, 2016).

Based on literature, modi­fication of lifestyle factors can delay onset of hypertension and can contribute to lowering of BP in treated patients (Gabb et al., 2016; Whelton et al., 2002). Systematic reviews have shown efficacy of interventions focused on physical inactivity (Pescatello et al., 2019; Smart et al., 2020) and dietary approaches to stop hypertension (DASH) (Filippou et al., 2020; Saneei et al., 2014; Siervo et al., 2015) in lowering BP among adults with or without hypertension in different settings. However, we do not know the acceptability of these behavioural interventions in the control of hypertension in Kenya. Clinical trials have also demonstrated the effectiveness of community based CHW interventions in lowering BP among both hypertensive patients(He et al., 2017; Jafar et al., 2010) as well as non-hypertensive population(T. H. Jafar et al., 2009; Neupane et al., 2018) in resource limited settings.

CHWs are an affordable and sustainable solution for behavioural intervention delivery, and an important linkage between community and health care system(Gilmore & McAuliffe, 2013). In light of critical shortages in the health workforce in LMICs, CHWs defined as members of a community with minimal formal training on health problems who provide basic health and medical care to their community, are increasingly recognized as an essential part of the health workforce needed to achieve public health goals (Jeet et al., 2017; Kok et al., 2015; Woldie et al., 2018; World Health Organization). However, the acceptability and effectiveness of CHW primary health intervention in the control of hypertension in Kenya has not been explored. Previous research conducted in Western Kenya demonstrated efficacy of CHW intervention in improving linkage to hypertension health care (Vedanthan et al., 2019) in the general population. However, the feasibility and acceptability of community based CHW lifestyle modification interventions in reduction of blood pressure in Kenya is not known. There is a need for further studies to support primary health interventions geared towards control of hypertension and CVD outcomes among hypertensive patients in the Nairobi metropolitan area. The current study proposes to test the acceptability and efficacy of a CHW-led lifestyle homebased intervention for BP reduction among hypertensive patients.

## 1.2 Significance

This study will not only provide an innovative approach to the management of hypertension through CHW primary health prevention but will also provide preliminary data on feasibility and acceptability of integrating CHW in the control of hypertension for a future fully- powered RCT. CHW have been used effectively in LMICs to deliver NCDs preventive services, using informational as well as behavioural approaches with focus on primordial prevention of NCDs and screening as part of early diagnosis and management. However, there is a lack of uptake of evidence-based community based CHW interventions for reduction of blood pressure in the Kenyan settings. While previous CHW hypertension interventions in LMIC have focused on screening and health education, the current study proposes to adapt a multicomponent evidence-based lifestyle intervention that incorporates behaviour communication and practical individualized lifestyle interventions to reduce BP and other CVD risks among low income population in Kiambu county.

## 1.3 Conceptual framework

# 2.0 RESEARCH QUESTIONS AND STUDY OBJECTIVES

## 2.1 Research Questions

The aim of this study is to explore innovative strategies to improve blood pressure and body composition through CHW lifestyle interventions for hypertensive patients in low income populations of Kiambu County, Kenya. Specific research questions are;

1. What is the prevalence of hypertension among adults in selected wards in Kiambu County?
2. What is the baseline cardio-metabolic risk among hypertensive patients in Kiambu County?
3. What is the effectiveness of a multicomponent CHW lifestyle intervention for control of BP among hypertensive patients in Kiambu County?
4. What is the acceptability of a multicomponent CHW lifestyle intervention for control of blood pressure among hypertensive patients in Kiambu County?

## 2.2 Broad Objectives:

To determine the feasibility and preliminary efficacy of a homebased intervention for the control and management of hypertension amidst the COVID-19 Pandemic in Kiambu County, Kenya

## 2.3 Specific Objectives

i. To determine the prevalence of hypertension among adults in selected wards in Kiambu County.

ii. To determine the baseline cardio-metabolic risk among hypertensive patients in Kiambu County.

iii. To determine the effectiveness of a multicomponent CHW lifestyle intervention for control of BP among hypertensive patients in Kiambu County.

iv. To determine the acceptability of a multicomponent CHW lifestyle intervention for control of blood pressure among hypertensive patients in Kiambu County.

# METHODOLOGY

3.1 Research design

This will be a randomized controlled trial (RCT). Hypertensive patient will be randomised to either CHW led lifestyle intervention or usual care arm. The intervention will be implemented for 6 months with outcome assessment at 3 and 6 months.

3.2 Study area

The study will be conducted in level 3 primary health care facilities in Juja and Ruiru Sub-counties in Kiambu County.

3.3 Study population

Patients with uncontrolled BP (systolic ≥140 mmHg and/or diastolic ≥90 mmHg measured on at least 2 separate screening measurements), and willing to be followed up for 6 months.

### 3.3.1 Inclusion criteria

Hypertensive individuals aged 18 years and above, receiving primary care from the participating Juja and Ruiru sub-counties.

### 3.3.2 Exclusion criteria

Elderly hypertensive patients aged above 70 years and hypertensive patients who wish to relocate from the study area during the study period will be excluded.

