## 3.5 Sampling and participants recruitment

We will randomly sample 2 wards in Ruiru and Juja Sub-counties. All participants in the selected wards with uncontrolled BP willing to participate will be recruited into the study. Screening will be done at the community level. CHW will conduct door to door screening for hypertension using digital BP machines for all adults in the selected wards. The CHW will document the BP readings and anthropometric measurement in a paper form register. The CHW will offer a referral letter (to the nearest level 3 hospital) for all participants with uncontrolled BP. The CHW will furnish the study coordinator with the particulars of such participants for follow-up and possible recruitment into the study. Participants will receive a refund of the transport cost upon presenting the referral note so as to encourage them to turn up at the health facility. Participants who do not show up in the facility within 48 hours of screening will be traced through home visits. The participants will be recruited for the RCT at the level 3 health facility in the respective wards after reassessment by the clinician and commencement of medical management.

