## 3.6 Data collection

An adapted WHO stepwise questionnaire will be used to collect information on demographic characteristics (age, sex, occupation), history of hypertension, other CVD risk factors, and health behaviours (smoking, alcohol drinking, diet, and physical activity) of participants at baseline and follow-up visits. The international physical activity questionnaire (IPAQ)(Craig et al., 2003) will be used to collect data on physical activity. The tools will be translated and validated in the local context. We will collect detailed data on patients care cascade during the home visits and monitor their ability to control their BP with the combination of medical management and the CHW intervention. Three BP measurements, body weight, height and waist circumference will be obtained at each data collection visit by outcome assessors masked to intervention assignment.

The primary outcomes will be the differences in systolic and diastolic BP changes from baseline to the end line survey. Secondary outcomes will include the proportion of patients with controlled hypertension (BP <140/90 mm Hg) ) according to the Kenyan national guidelines(Division of Non-Communicable Diseases-Ministry of Health, 2018), body composition – Body mass index(BMI), waist circumference . Low physical activity will be defined as less than 150 minutes of moderate physical activity or 75 minutes of vigorous activity each week. To assess the outcome of the intervention the survey conducted at baseline will be conducted at 3 months of follow-up and at the end of 6 months of intervention.

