|  | *The last question is about the time you spent sitting on weekdays during the last 7 days. Include time spent at work, at home, while doing course work and during leisure time. This may include time spent sitting at a desk, visiting friends, reading, or sitting or lying down to watch television*.  During the last 7 days, how much time did you spend sitting on a week day? | 1.…………… hours per day  2……………. minutes per day  Don’t know/Not sure |
| **History of Raised Blood Pressure** | | |
|  | Have you ever had your blood pressure measured? |  |
|  | Have you ever been told by a doctor or other health worker that you have raised blood pressure or hypertension? |  |
|  | Are you on any treatments/advice for high blood pressure? | |
|  | Drugs (medication) that you have taken in the past two weeks |  |
|  | Advice to reduce salt intake |  |
|  | Advice or treatment to stop smoking |  |
|  | Advice to start or do more exercise |  |
| **Step 2 Physical Measurements** | | |
|  | Interviewer ID |  |
|  | Device IDs for height and weight |  |
|  | Height(cm) |  |
|  | Weight(kg) |  |
|  | **For women:** Are you pregnant? |  |
|  | Waist circumference(cm) |  |

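### Pregnancy is asked about on the survey form but is not an exclusion, so pregnant women can be randomised and add avoidable noise, mainly to BMI and waist

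*Protocol*

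**What the plan says.** Entry is broad. Section 3.3.1 takes "Hypertensive individuals aged 18 years and above, receiving primary care from the participating Juja and Ruiru sub-counties". Section 3.3 adds uncontrolled BP (systolic at least 140 and/or diastolic at least 90 mmHg on at least two separate screening measurements) and willingness to be followed for 6 months. Section 3.5 describes door-to-door screening of adults and states: "All participants in the selected wards with uncontrolled BP willing to participate will be recruited into the study".

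Section 3.3.2 gives the only exclusions: "Elderly hypertensive patients aged above 70 years and hypertensive patients who wish to relocate from the study area during the study period will be excluded".

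Pregnancy is mentioned once in the document. In the physical measurements part of Appendix 2, between weight and waist circumference, women are asked "Are you pregnant". No instruction follows the item. Section 3.9 does not name pregnancy among the adjustment variables.

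The outcomes are changes over follow-up. Section 3.6 states: "The primary outcomes will be the differences in systolic and diastolic BP changes from baseline to the end line survey". The secondary outcomes include BP control and "body composition – Body mass index(BMI), waist circumference". On timing, section 3.1 states: "The intervention will be implemented for 6 months with outcome assessment at 3 and 6 months".

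**The concern.** The form foresees that some women will be pregnant, but no eligibility rule uses the answer. A pregnant woman over the BP threshold satisfies the written criteria and can be allocated to either arm.

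Over 6 months she will either deliver or move well along in the pregnancy. Her weight and waist will then change mostly for that reason, whichever arm she is in. Her BP may also follow a different course from that of the other participants, though the effect there is smaller. The direction depends on the stage at entry: a woman recruited late and delivered before end line shows a fall in weight and waist, while one recruited early shows a rise.

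What is at stake is precision and the chance of an uneven split between two small arms. Body composition is the most exposed outcome. Eligibility belongs in the protocol, and an analysis plan written later cannot undo a randomisation.

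**Working it through.** **1. Reading the criteria against the form.**

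| Place in the Protocol | What it does with pregnancy |
|---|---|
| 3.3 and 3.3.1 (population, inclusion) | Nothing; adults of either sex from 18 |
| 3.3.2 (exclusion) | Nothing; only age above 70 and planned relocation |
| 3.5 (recruitment) | Nothing; a clinician reassesses before recruitment, with no pregnancy rule stated |
| 3.6 (outcomes) | Nothing |
| 3.9 (analysis) | Not named; baseline characteristics are left open |
| Appendix 2 (form) | Asks; no consequence attached |

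Section 3.8 puts the baseline assessment before randomisation, so the answer can be in hand before allocation.

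**2. The plan's own figure.** Section 3.4 gives 52 in total for Cohen's d = 0.80, two-sided 0.05 and 80% power. The normal approximation, n per arm = 2(1.960 + 0.842)²/0.80² = 24.5, rounds up to 25, or 50 in total. The two-sample t-test needs 25.52, so 26 per arm and 52 in total, which matches. Power at 26 per arm is 80.7% (t-test). The allocation ratio is not stated; 26 per arm assumes 1:1.

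**3. One woman's effect on her arm's mean.** Shift = (her extra change)/26. The extra changes are assumptions, not figures from the Protocol, for a woman recruited in late pregnancy and delivered before end line.

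- Waist, 20 cm fall: 20/26 = 0.77 cm.
- BMI, 10 kg lost at 1.60 m: 10/1.60² = 3.9 kg/m²; 3.9/26 = 0.15 kg/m².
- Systolic BP, extra fall of 5 to 15 mmHg: 5/26 = 0.19 to 15/26 = 0.58 mmHg.

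Two such women in one arm double these figures. For a yes/no outcome such as BP control, one woman whose status changes moves the arm's proportion by 1/26 = 3.8 percentage points.

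**4. Scale against the target effect.** With an assumed SD of 12 to 20 mmHg, d = 0.80 is 9.6 to 16 mmHg. The upper BP shift of 0.58 mmHg is then 0.58/16 = 4% to 0.58/9.6 = 6% of it.

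**5. Effect on power for BP.** Suppose k of the 52 are pregnant and their BP change is shifted by m SD regardless of arm. With p = k/52, the SD is inflated by √(1 + p(1−p)m²). Both k and m are assumed.

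| k | m (SD) | SD inflation | Power for d = 0.80 |
|---|---|---|---|
| 0 | – | 1.000 | 80.7% |
| 1 | 0.5 | 1.002 | 80.6% |
| 2 | 1 | 1.018 | 79.3% |
| 3 | 2 | 1.103 | 72.7% |
| 5 | 2 | 1.161 | 68.3% |

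**6. Chance imbalance.** If all k fall in one arm, the group difference moves by k·m/26 SD: 2 × 1/26 = 0.08 SD, or 3 × 2/26 = 0.23 SD. The chance that all fall in the same arm is 25/51 = 49% for k = 2 and (25/51)(24/50) = 24% for k = 3.

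**The case against.** The strongest reply is that this hardly touches the primary outcome. Pregnancy at baseline is balanced by randomisation in expectation, the primary comparison is between arms, and similar shifts in both arms largely cancel. One woman moves mean systolic BP by well under 1 mmHg. Clear loss of power needs three to five women with a 2 SD shift, and nothing in the Protocol supports such numbers. All of this stands, and it limits the point to noise and chance imbalance.

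Second, a clinician reassesses patients and starts treatment before recruitment (section 3.5), and may divert pregnant women. That is possible, so it would be wrong to infer that such a woman is certain to be randomised. But no pregnancy rule is stated there, so the gap stays open.

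Third, the pregnancy item is on a survey repeated at 3 and 6 months, and the adjustment for baseline characteristics could take it in. How weight and waist are handled for a pregnant woman is commonly left to the analysis plan. This holds for analysis, but not for eligibility. Asking the question without excluding on it is also no contradiction in itself, since the form serves to describe risk factors.

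A reader might also infer a safety problem from the physical activity programme. The Protocol gives no basis for that: it states no risk from the programme, and describes it as individualised, with tailored counselling. The point does not rest on safety.

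**Conclusion.** The point holds as a cheap improvement to eligibility. As written, the criteria let a pregnant woman into the randomised comparison, and her own change in BMI and waist, and in part BP, would largely reflect pregnancy or delivery.

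A reader might go further and conclude that the trial's result is biased, or would reflect pregnancy instead of the programme. The documents do not support that: allocation is random, so what remains is added variance and the possibility of an uneven split.

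Per affected woman, the size is modest for body composition and small for BP. These figures rest on assumed changes for a late-pregnancy case and on 1:1 allocation. The number of pregnant participants is not given and may be zero. The case for acting is the clear gap and the very low cost, not a large expected effect on the primary outcome.

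**What to change.** In section 3.3.2, add current pregnancy at baseline, by the answer to the question already in Appendix 2, as an exclusion from the randomised comparison. State that home screening, referral for care and the count for the prevalence objective are unchanged.

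Keep women who become pregnant after randomisation in the primary analysis, and leave the handling of their BMI and waist to the analysis plan. A rule that sets their values to missing, or drops them, would itself create outcome-related missing data or a post-randomisation exclusion, and is not needed here.

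The cost is one line of text and no new data item. The downside is that a few screened women do not enter the trial.

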## 3.8 Study procedure

The study coordinator and the research assistants will complete a baseline assessment for the illegible participants. This will involve a survey to collect sociodemographic variables, measuring BP, anthropometric measurements (Height, weight and waist circumference) and lifestyle behaviour. Patients with uncontrolled blood pressure will be randomized either control arm (usual care) or intervention arm (Figure 1). The intervention will include a multicomponent community health worker–led home intervention (health coaching, home BP monitoring, BP audit and feedback, physical activity program to be implemented over a period of six (6) months. Participants randomized to the intervention will receives 2 home visits by the trained CHW over a period of 1 month, followed by monthly follow-up visits for a period of 6 months. The initial visit will involve a 90-minute home visit to discuss general knowledge about hypertension and offer tailored counselling on lifestyle modification as well as set physical activity targets. Subsequent monthly visit will be focused on social support, goal setting, problem solving, and maintaining motivation to meet set targets. The visits will involve BP monitoring during which the client and CHW will evaluate the BP and physical activity targets.

To assess the outcome of the intervention the survey conducted at baseline will be conducted by two trained research assistants (who were not part of and have no relationship with the CHWs team) to evaluate the participants at 1) 3 months and 2) 6 months when the intervention has ended. The research assistants will be blinded to the randomization status of the participants. The home visits/clinic visit for evaluation will be scheduled during the first half of the day to minimize the effect of diurnal variations in BP.

Materials to be used will include automatic BP machine, tape measure, a bathroom weighing scale, smart watch fitness monitor and a smart phone with intervention protocol detailing the health education on lifestyle intervention for reducing BP. A paper-based protocol will also be provided for back-up.

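### The clinician reassessment before recruitment is not required to decide whether a patient is safe for the physical activity targets, and the eligibility rules contain no upper BP limit or medical exclusion

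*Protocol*

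**What the plan says.** Section 3.3 defines the population by systolic BP of at least 140 mmHg and/or diastolic BP of at least 90 mmHg, "measured on at least 2 separate screening measurements". Section 3.3.1 adds age 18 or over and local primary care. Section 3.3.2 completes the rules: "Elderly hypertensive patients aged above 70 years and hypertensive patients who wish to relocate from the study area during the study period will be excluded".

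On recruitment, section 3.5 states: "All participants in the selected wards with uncontrolled BP willing to participate will be recruited into the study". The same section places recruitment at the level 3 facility "after reassessment by the clinician and commencement of medical management".

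Section 3.8 then states: "Patients with uncontrolled blood pressure will be randomized either control arm (usual care) or intervention arm". The intervention has four listed parts, one of which is a physical activity programme. Intervention patients receive "2 home visits by the trained CHW over a period of 1 month", then monthly visits. At the initial visit the CHW is to "offer tailored counselling on lifestyle modification as well as set physical activity targets". Later visits include BP checks and a review of the targets. The materials include "a smart phone with intervention protocol detailing the health education on lifestyle intervention for reducing BP". Section 3.7 describes the activity programme as individualised.

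**The concern.** An activity target is a prescription, and here it is given to people chosen because their BP is not controlled. The person who sets it is a CHW, a group that section 1.1 describes as having little formal health training. One would expect a stated clinical decision that activity is safe before that happens, either as an eligibility rule or as a defined output of the clinician's visit. The protocol has neither.

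What is at stake is patient safety. Followed as written, the rules let a patient whose severe BP has not yet come down, or who has had a recent cardiovascular event, be randomised and given an activity target without anyone being required to decide that this is safe. The BP comparison between arms is not at issue.

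**Working it through.** The point rests on the text, so the check is to follow a patient through the stated rules.

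**Step 1: the entry rules.** Take two patients aged 18 to 70 in local primary care, willing to join and not planning to move. Patient A has severely raised BP. Patient B has BP just over the threshold and a recent cardiovascular event.

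| Rule | Patient A | Patient B |
|---|---|---|
| BP at or above 140 and/or 90 mmHg (3.3) | met | met |
| Age 18 or over, local primary care (3.3.1) | met | met |
| Excluded if above 70 or moving away (3.3.2) | not excluded | not excluded |
| All willing people with uncontrolled BP are recruited (3.5) | recruited | recruited |

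No rule separates either of them from a patient at low risk.

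**Step 2: the clinician contact (3.5).** Two things are stated: the patient is reassessed, and medical management begins. Three things are not stated: that the reassessment covers activity, that severe BP must come down first, and that the clinician may hold a patient back. Starting treatment does not establish that BP has fallen, and section 3.8 confirms that patients are randomised while BP is uncontrolled.

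**Step 3: the activity target (3.8).** It is set at the initial home visit, and two visits fall within one month. No clinician input to the target is stated, and no BP level is given at which the CHW should withhold activity or refer back.

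**Step 4: other places where a rule might sit.** The ethics section (3.10) contains no safety screening. The questionnaire in Appendix 2 asks about pregnancy, but no rule uses the answer. A statistical analysis plan would not normally supply eligibility or medical exclusions.

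**Step 5: effect on the sample size.** The planned figure reproduces. With d = 0.80, two-sided 0.05 and 80% power, the normal approximation gives 2(1.960 + 0.842)² / 0.80² = 24.5, so 25 per arm. The exact two-sample t-test gives 25.5, so 26 per arm and 52 in total, with power 0.807. Nothing in the point changes this.

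The documents do not say how many patients would be held back. If a proportion p were held back and never cleared (assumption), the number of otherwise eligible patients needed to randomise 52 is 52/(1 − p), rounded up:

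- p = 1%: 52/0.99 = 52.5, so 53
- p = 5%: 52/0.95 = 54.7, so 55
- p = 10%: 52/0.90 = 57.8, so 58

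Patients cleared later would reduce the extra number needed.

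**The case against.** The strongest reply is that section 3.5, read whole, already puts a clinician between the doorstep and the trial. Screened people are passed to the coordinator as possible recruits only, those who do not attend within 48 hours are traced at home, and treatment begins before entry. Counselling is tailored, targets are individualised and BP is checked at visits. The CHW's intervention protocol is not shown and may hold cautions. Figure 1, which the randomisation sentence cites, is not shown either. Activity is one of four components, so excluding anyone unfit for exercise would deny them the chance of the other three. Finally, a check after allocation but before the first target would protect the same patients.

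Much of this stands. It makes the gap small, and it rules out a remedy that excludes everyone with an activity restriction. It does not close the gap. The clinician's contact has no stated decision attached to it, and the CHW's material operates only once a patient has been allocated. A later check could make the target safe, but it could not keep an acutely unfit patient from being randomised. Using the existing contact also means that the same judgement is made in both arms without knowledge of the allocation.

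A reader might infer that untreated patients go straight from screening to exercise. Section 3.5 contradicts that. A reader might also take the low treatment rate quoted in section 1.1 as a measure of how many patients are at risk. It bears on how many would be new to treatment, which is a different quantity, and it comes from a national survey, whereas these patients are already in primary care.

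**Conclusion.** The point holds as a limited patient-safety gap. The eligibility rules have no upper BP limit and no medical exclusion, and the clinician who sees every patient is not required to judge whether the activity targets are safe. The stated rules therefore allow a patient with severe BP or a recent cardiovascular event to receive a target without a clinical decision.

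Its size cannot be put as a number: the documents give neither a count of unsafe patients nor a rate of harm from the activity programme. A reader might infer a biased comparison or lost power. Neither follows, since the rules apply before allocation and the sample size is unaffected. Nor do the documents show that clinicians would fail to screen in practice or that the CHW's material lacks cautions. The conclusion is only that the protocol does not require the decision. It assumes that the unseen Figure 1 contains no such step. The change is worth making because it is cheap and improves safety.

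**What to change.** - **Section 3.5:** state that at the reassessment, before allocation, the clinician records for every patient whether physical activity is safe, needs a limit, or must wait. For patients allocated to the intervention, the CHW sets no activity target beyond that record.
- **Section 3.3.2:** add that a patient whom the clinician judges acutely unfit, for example because of severe BP needing urgent treatment or a recent cardiovascular event, is not randomised until cleared.
- **Section 3.5, recruitment sentence:** make the statement that all willing participants are recruited subject to this rule.
- **Patients who need only a reduced or nil activity target:** state that they stay eligible and, if allocated to the intervention, receive its other components.

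The cost is one recorded judgement at a contact that already takes place, and a slightly narrower randomised population. The sample size stays at 52. If 1% to 5% were held back and never cleared (assumption), one to three more otherwise eligible patients would have to be found.
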